## Abstract

**Background:**

Chronic hepatitis B (CHB) can progress to cirrhosis, hepatocellular carcinoma (HCC) and ultimately liver-related death. Although oral antiviral therapy for patients with CHB reduces the risk of such complications, once cirrhosis is established, the benefits of antiviral therapy are not robustly demonstrated. According to traditional Chinese medicine (TCM), some Chinese herbal medicines promote blood circulation and soften hard masses, and therefore they may block and reverse hepatic fibrosis. The aim of this study is to evaluate the effects of TCM tablets of the compound *biejia ruangan* (RGT) administered for fibrosis, and entecavir (ETV), on the development of HCC in patients with CHB or hepatitis B virus (HBV)-related compensated cirrhosis.

**Methods/design:**

This multicenter, centrally randomized, double-blind, placebo-controlled, parallel-group study is planned to complete within 5 years. For the study, 1,000 with CHB or HBV-related compensated cirrhosis are randomly assigned in a 1:1 ratio to a treatment group (0.5 mg ETV once daily; 2 g RGT three times daily) or a control group (0.5 mg ETV once daily; 2 g RGT dummy agent three times daily). The primary end points are the development of HCC and liver-related death. Secondary end points include disease progression and overall survival.

**Discussion:**

Although antiviral therapy can achieve sustained suppression of HBV replication, thereby preventing cirrhosis, patients with CHB treated with nucleos(t)ide analogs (NUCs) retain a higher risk for HCC compared with patients with inactive disease. Although previous clinical trials with RGT have confirmed the efficacy of blocking and reversing hepatic fibrosis in patients with CHB or compensated cirrhosis, the long-term risk for HCC or disease progression in these patients treated with combination of RGT and NUCs compared with NUCs alone is unclear. Therefore, it is necessary to investigate the effects of the RGT blockade and reversal of hepatic fibrosis on the development of HCC in patients with CHB or HBV-related compensated cirrhosis in large, prospective, multicenter, double-blind, randomized, controlled trials in China.

**Trial registration:**

ClinicalTrials.gov Identifier: NCT01965418. Date registered: 17 October 2013

## Background

Hepatitis B virus (HBV) infection is a major health problem worldwide with an estimated 350 million chronic carriers [1], and carriers in China account for 33% of all chronic carriers globally [2, 3]. Although treatment of chronic hepatitis B (CHB) has dramatically improved over the past decade, chronic HBV infection is still the most common underlying cause of hepatocellular carcinoma (HCC), which remains one of the most common cancers worldwide. A large longitudinal epidemiological study of the natural history of patients with chronic HBV infection has shown that baseline HBV DNA level or cirrhosis is an independent predictor for the development of HCC [4].

Although antiviral therapy can theoretically prevent HCC by inhibiting HBV replication and preventing the development of, or even reversing, cirrhosis, in patients with fibrosis or cirrhosis, eradication or suppression of HBV does not remove this risk and occurrence of HCC, but can control the complications and gain time to prepare for liver transplantation [5–7]. Antiviral therapy has minimal side effects and sustained suppression of HBV replication can be achieved, thus preventing such complications. However, patients with CHB treated with nucleos(t)ide analogs (NUCs) retain a higher risk for HCC compared with patients with inactive stage disease [8].

According to traditional Chinese medicine (TCM), Chinese medicines promoting blood circulation and softening hard masses may be appropriate for blocking and reversing hepatic fibrosis in CHB or CHB-related compensated cirrhosis. Over the past decade, the role of TCM in the treatment and prevention of fibrosis has been confirmed by a growing number of experiments and clinical studies [9]. To date, no randomized clinical trial (RCT) has reported whether TCM (tablets of the compound *biejia ruangan*; RGT) administered to block and reverse hepatic fibrosis in CHB or HBV-related compensated cirrhosis decreases the risk of developing HCC. RGT (Inner Mongolia Furui Medical Science Co Ltd, Wulanchabu, China) was the first antifibrotic herb approved by the Chinese Food and Drug Administration (CFDA) for fibrotic liver disease in China. The main components of RGT are: turtle shell, zedoray rhizome, peony root, *Angelica sinensis*, pseudo-ginseng, campanumaea pilosula, *Astragalus*, dried human placenta, plant worms, *Baphicacanthus* root and farsythio (Table 1). RGT can soften hardness to dissipate stagnation, and disperse blood stasis and detoxification, and enhance *qi* (biological substances or activities that preserve life) and blood. Syndromes in Chinese medicine include: (1) weakening of both *qi* and blood, (2) blockage of meridians (circulation channels for *qi*) by blood stasis and (3) generation of dampness and heat (inflammatory pathogens). All composites in this prescription are commonly used clinically for chronic liver disease, to soften hard masses and dissolve stagnation, and at the same time, to secure essence and eliminate evil. The quality of the herbal drugs was controlled as follows. First, as a specific treatment of liver fibrosis and early cirrhosis, RGT was approved by the CFDA in 1999, with the license number Z1999101. Second, all the components of RGT are purchased from designated and certificated herb plantations. None of these herb providers has changed during the past 10 years. Third, the production workshops for RGT are also certified by the Good Manufacturing Practices standard. No serious adverse effects have been reported even though the drug entered the market >15 years ago. Finally, RGT has passed the Good Clinical Practice (GCP) certification by the CFDA, which is the internationally recognized standard for the design, conduct, recording and reporting of clinical trials involving human subjects.

**Table 1 Tab1:** **The major ingredients of**
***fufang biejia ruangan pian***
**(RGT)**

Chinese phonetic alphabet name	Latin name	English name
*Biejia*	*Carapax trionycis*	Turtle shell
*Ezhu*	*Rhizoma curcumae*	Zedoray rhizome
*Chishao*	*Radix Paeoniae rubra*	Peony root
*Danggui*	*Radix Angelica sinensis*	*Angelica sinensis*
*Sanqi*	*Radix notoginseng*	Pseudo-ginseng
*Dangshen*	*Radix codonopsis*	Campanumaea pilosula
*Huangqi*	*Radix astragali*	Astragalus
*Ziheche*	*Placenta hominis*	Dried human placenta
*Dongchongxiacao*	*Cordyceps sinensis*	Plant worms
*Banlangen*	*Radix isatidis*	Baphicacanthus root
*Lianqiao*	*Fructus forsythiae*	Farsythio

Some clinical trials have demonstrated that RGT can block the development of hepatic fibrosis and reverse early cirrhosis [10]. Other studies have shown that RGT can significantly improve compensated cirrhosis, especially in CHB and early cirrhosis, with a total rate of effectiveness of 81.67%; after a 1-year follow-up, the total rate of efficacy was shown to be 76.85% [11]. Yang *et al*. [12–14] have reported that RGT significantly blocks early liver fibrosis, inhibiting the proliferation of hepatic stellate cells, reducing collagen synthesis and excess deposition in the space of Disse, dissolving and absorbing formed collagen fibers, and inhibiting expression of collagen α2 (I) mRNA. It has also been shown that RGT increases the phagocytic function of macrophages in the abdominal cavity of mice. Zhao *et al*. [15] have reported similar results, and have proposed that RGT has antifibrotic efficacy through interaction with multiple targets that affect hepatic fibrosis. Some studies have confirmed that RGT has better antifibrotic efficacy in compensated cirrhosis [16, 17], especially HBV-related hepatic fibrosis [18].

Although some studies have concluded that RGT can block and reverse hepatic fibrosis in CHB, there are limited data on preventing or delaying the development of HCC in the treatment of CHB or HBV-related compensated cirrhosis. To address this issue, we are conducting a large, prospective, multicenter, centrally randomized, double-blind, controlled trial to establish whether RGT can prevent or delay the development of HCC by blocking and reversing hepatic fibrosis in CHB or HBV-related compensated cirrhosis. The aims of this clinical trial are: (1) to evaluate the effect of combined application of RGT and entecavir (ETV) on development of HCC in patients with CHB or HBV-related compensated cirrhosis and (2) to evaluate the efficacy of combined application of RGT and ETV in preventing or delaying the incidence of decompensated cirrhosis and disease progression in the treatment of patients with CHB or HBV-related compensated cirrhosis.

## Methods/design

### Study design

This large, prospective, multicenter, centrally randomized, double-blind, placebo-controlled trial is being conducted in nine institutions between November 2013 and November 2018. The study meets the requirements of the Declaration of Helsinki, and has been approved by the ethics committees of each participating institution. All patients with CHB or HBV-related compensated cirrhosis are carefully screened by a multidisciplinary team to select suitable candidates for this clinical trial, according to the inclusion and exclusion criteria of the present RCT and the patients’ willingness to participate in the study. For the study, 1,000 patients are being randomly assigned in a 1:1 ratio to one of two groups: a treatment group (0.5 mg ETV once daily; 2 g RGT three times daily) or a control group [0.5 mg ETV once daily; 2 g RGT dummy agent (similar in taste, shape and color to RGT; main ingredients include pearl barley and grilled germinate barley) three times daily]. During the double-blind phase, unblinding will take place as soon as sufficient evidence indicates: (1) that the effect of RGT plus ETV blocking and reversing hepatic fibrosis (measured by METAVIR system) is statistically superior to that with ETV alone, (2) that RGT plus ETV does not provide a significant advantage over ETV alone by the second liver biopsy at week 72 of double-blind treatment or (3) safety concerns. Patients who reach an end point are offered open-label RGT plus ETV or ETV alone for 1 year, and patients who have blockade and reversal of hepatic fibrosis are followed up after treatment and have the option to receive RGT plus ETV as an open-label treatment in the event of hepatic fibrosis or necroinflammatory progression. However, patients with stable or reversed disease will continue to receive antiviral therapy with ETV alone, but those with disease progression will receive open-label RGT plus ETV as in the control group. The study will be terminated as soon as sufficient evidence indicates that the outcome of patients with CHB or HBV-related compensated cirrhosis by RGT plus ETV blockade and reversal of hepatic fibrosis is statistically superior to that with ETV alone or does not provide a significant advantage over ETV. If the trial is terminated according to the predefined criteria, patients will be offered open-label treatment for 1 year. Liver biopsies are performed at three defined time points: before the start of randomization (pretreatment), at week 72 of the double-blind treatment, and at month 24 of the open-label treatment in the follow-up study. After 24 weeks of treatment, any patients with a reduction in HBV DNA level from baseline <1 log IU or 2 log copies/mL will be treated with a combination of ETV and adefovir dipivoxil (10 mg once daily) against HBV. The flow chart of the study is shown in Figure 1.

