### Sample size

We assumed that the rate of hepatic fibrosis reversal would be 39% in the ETV-treated patients at the end of 2 years [26, 27], and 61% in the RGT-treated patients. Using PASS 2002 statistical software (NCSS, Kaysville, UT, USA), we calculated that we need two groups of 186 cases, and each group needs to enroll 223 cases if there is a drop-out rate of 15%, that is, a total of 446 cases. Currently, up to 45% of all enrolled patients will be accepted for a second liver biopsy. A total of 500 cases is required in each group to achieve a power of 0.80 and a significance level of 0.05 in assessing the difference between the two groups.

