### Data and safety monitoring board

To promote consistent study execution at each participating center, independent monitoring visits are performed to supervise trial progress, ensuring that it is conducted, recorded and reported in accordance with the protocol, standard operating procedures, GCP and the applicable regulatory requirements.

The Data and Safety Monitoring Board consists of three independent hepatologists who are not members of the end-point committee and an independent statistician. The board protects the ethical interests and safety of the patients by reviewing interim analyses. The board is empowered to recommend termination of the study on the basis of safety concerns or as soon as sufficient evidence indicates that RGT plus ETV is statistically superior to ETV alone, or that RGT plus ETV does not provide a significant advantage over ETV alone.

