### Statistical methods

The randomized subjects who have taken at least one dose of study drug and are evaluated for at least once curative effect after taking medication, constitute the full analysis set and safety analysis set. Those who complete all the visits comprise the per-protocol set. The statistical analysis will be performed using SAS 9.1 software (SAS Institute, Cary, NC, USA). The overall loss rate due to adverse events of each group will be calculated. When subjects enter the trial, they are assessed for demographic data, baseline condition and other essential information and are compared between groups. Cumulative incidence of HCC and overall survival rate will be determined by Kaplan–Meier analysis, and the log-rank test will be used for treatment comparisons. Changes from baseline in liver histology (METAVIR score) as well as in liver and spleen imaging (type B ultrasound) between the two groups will be compared by the Cochran–Mantel–Haenszel test. Changes from baseline in serum markers for liver fibrosis and liver function, transient electrograph (FibroScan) and TCM syndrome between the two groups will be compared by a covariance or non-parametric test. The statistical significance is defined as a two-sided *P* <0.05.

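### The two efficacy triggers for unblinding are complementary and rest on week-72 histology, so no histology result lets the blinded comparison of HCC or liver-related death continue

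*Protocol article*

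**What the plan says.** All references are to the protocol article.

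- **Study design, unblinding.** Three grounds are listed. The first is "that the effect of RGT plus ETV blocking and reversing hepatic fibrosis (measured by METAVIR system) is statistically superior to that with ETV alone". The second is "that RGT plus ETV does not provide a significant advantage over ETV alone by the second liver biopsy at week 72 of double-blind treatment". The third is safety. The list is introduced as something that will happen once the evidence is sufficient; no numerical criterion is given.
- **Study design, termination.** The study ends when there is enough evidence that patient outcome is superior with the combination, or that the combination has no significant advantage. No time point is attached. The criteria are called predefined but are not set out.
- **Data and safety monitoring board.** The board reviews interim analyses and may recommend termination on safety grounds. Its efficacy grounds are worded "as soon as sufficient evidence indicates that RGT plus ETV is statistically superior to ETV alone, or that RGT plus ETV does not provide"; what is then named as lacking is significance of the benefit.
- **Study design, open-label provisions.** Patients with stable or reversed disease continue on ETV alone, while "those with disease progression will receive open-label RGT plus ETV as in the control group". The third biopsy is at month 24 of open-label treatment.
- **End points (under Study design).** The primary end points are HCC or liver-related mortality. Histology enters only through the secondary end point of disease progression.
- **Statistical methods.** The one threshold given is general: "The statistical significance is defined as a two-sided *P* <0.05".

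**The concern.** A rule for opening the codes should leave at least one result under which blinding continues. Here, superior and not significantly better together cover every histology result. The rule therefore does not decide whether to unblind; it fixes roughly when.

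The end point is also mismatched. A biopsy result decides whether the comparison of HCC and liver-related death stays blinded. That matters for ascertainment: surveillance is every 3 or 6 months, clinical diagnosis of HCC depends on which imaging is done, and liver-related death requires a judgement of cause. Once treatment is known, each can differ by arm. If later RGT exposure follows fibrosis status rather than randomisation, the contrast between arms also shrinks.

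Finally, the termination wording treats absence of significance as a reason to stop. Early in a trial with few events, a non-significant result is expected even when the treatment works, so it says little about futility.

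**Working it through.** **1. Are the triggers complementary?** Let S be the event that the week-72 histology comparison is significant in favour of RGT plus ETV. Trigger 1 is S and trigger 2 is not-S, so P(trigger 1) + P(trigger 2) = 1 at any threshold. A result significantly favouring ETV alone also falls under trigger 2.

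Illustration with the article's figures: 39% and 61% reversal, 45% of 500 = 225 second biopsies per arm, and two-sided 0.05 (the threshold at this read is an assumption, and the rates are stated for 2 years, not week 72). With pooled variance under the null:

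- SE under the null = √(2 × 0.5 × 0.5 / 225) = 0.0471
- SE under the design rates = √((0.39 × 0.61 + 0.61 × 0.39) / 225) = 0.0460
- P(S) = Φ((0.22 − 1.96 × 0.0471) / 0.0460) = Φ(2.77) = 0.997, so P(not-S) = 0.003
- With no effect, P(S) = 0.025 and P(not-S) = 0.975

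Both pairs sum to 1.

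**2. Is there a plan figure for the primary end point?** No. The Sample size section concerns fibrosis reversal only. Its last step reproduces (223 / 0.45 = 496, stated as 500). The 186 per group does not follow from 39% versus 61% at 80% power and two-sided 0.05, which needs 80 per group; that is a separate matter and is not used here. No HCC rate, hazard ratio or event target is stated, so step 3 rests on assumptions.

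**3. What does the blinded period hold for the primary end point?** Assumptions: control hazard r of 1-4% per year, hazard ratio 0.70, 500 per arm, no dropout, 72 weeks = 1.38 years of follow-up per patient.

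- Events = 500(1 − e^(−rT)) + 500(1 − e^(−0.70rT))
- Power = Φ(½ × √events × |ln 0.70| − 1.96), with |ln 0.70| = 0.357

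| Control rate per year | Events, 72 weeks | Power | Events, 5 years | Power |
|---|---|---|---|---|
| 1% | 6.9 + 4.8 = 12 | 9% | 24.4 + 17.2 = 42 | 21% |
| 2% | 13.6 + 9.6 = 23 | 14% | 47.6 + 33.8 = 81 | 36% |
| 3% | 20.3 + 14.3 = 35 | 18% | 69.6 + 49.8 = 119 | 50% |
| 4% | 26.9 + 19.0 = 46 | 23% | 90.6 + 65.3 = 156 | 61% |

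The 5-year columns are an upper limit, because recruitment falls inside the five years. For reference, 80% power at this hazard ratio needs (1.96 + 0.84)² × 4 / 0.357² ≈ 247 events.

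**The case against.** **The wording leaves room.** Every trigger requires sufficient evidence, so an undecided state is conceivable, and the board only recommends. This stands as a softening: one cannot say that termination is certain. It does not rescue trigger 2, which is tied to the week-72 biopsy. A fuller protocol or board charter could add boundaries, but it could not make room between two complementary conditions without contradicting this text.

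**Unblinding and termination are different rules.** This stands. The week-72 time point belongs only to the second unblinding trigger. The termination sentence refers to patient outcome and the board section names no end point, so histology is not shown to be the basis for stopping the trial.

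**HCC follow-up does not stop at week 72.** This stands. Data collection runs to November 2018. With staggered entry, an aggregate read could also give early patients more than 72 blinded weeks, so 72 weeks per patient is an illustration, not a cap.

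**Low power is not mainly due to this rule.** This stands in part: the 5-year columns are also low at most of the assumed rates.

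**A stronger reading to avoid.** A reader might infer that interim looks use P<0.05 unadjusted, and so expect a type I error of about 8-14% for two to five looks. The article states a general threshold and does not apply it to interim looks; boundaries may be set elsewhere. Nor does that reading fit a rule under which the first look would already satisfy one stopping ground. A histology look does not by itself inflate the error of the HCC log-rank test, and stopping for no advantage does not inflate it at all.

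**Conclusion.** The point holds for the rule as stated. The two efficacy grounds for unblinding exhaust the possible results of the week-72 histology analysis, and they rest on an outcome other than the primary one. The termination sentence and the board's remit also accept non-significance alone as a ground to stop. This follows from the wording and needs no numerical assumption.

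The consequence is the loss of a blinded comparison free of cross-treatment from about the week-72 read, not the loss of all HCC data. Its size depends on rates that the article does not give. At 1-4% per year and a hazard ratio of 0.70, power for the blinded part is 9-23%, against at most 21-61% over five years. The documents do not support a claim that the trial must terminate at week 72 or that unadjusted interim testing is planned.

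**What to change.** 1. **Unblinding.** Do not let the week-72 histology result alone (grounds 1 and 2) open the treatment codes to sites and outcome assessors. An independent statistician can analyse it by arm for the board.
2. **Termination.** Replace the no-significant-advantage ground with a defined, non-binding futility criterion on HCC or liver-related death. Tie stopping for superiority to the same end point, with a prespecified interim boundary. Use the same wording in Study design and in the board section.
3. **Safety.** Leave all safety grounds for unblinding and termination as they are.
4. **Analysis.** Analyse HCC and liver-related death by randomised arm regardless of later open-label treatment.
5. **Open-label passages.** Keeping the codes closed does not by itself prevent mixing of the arms. The open-label provisions and the third-biopsy timing must be reconciled with the blinded primary comparison; which treatment rule applies is for the trial team to settle.

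**Cost.** This means an amendment to the protocol and board charter while the trial is recruiting. Histology results by arm would be released later, and the final critical P may fall slightly below 0.05. Items 1, 2 and 4 are mainly changes of wording; item 5 may touch the design, because the article already plans a long open-label phase.

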### Follow-up

At baseline, all patients are screened to confirm the absence of HCC using abdominal ultrasonography and laboratory analyses, including AFP level. During the follow-up, all patients are seen at 3- to 6-month intervals. Periodic surveillance is also performed with abdominal ultrasonography and laboratory analyses, including AFP level, every 3 or 6 months to screen for HCC and other complications related to portal hypertension. Patients also undergo endoscopy every 1 or 2 years for screening and follow-up of gastroesophageal varices. HBV DNA, hepatitis B surface antigen (HBsAg), anti-HBs, hepatitis B e antigen, anti-HBe, and routine hematological and biochemical tests are performed. Adverse events that have occurred since the previous visit are recorded, and toxicity is graded according to predefined criteria.

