### Participants and eligibility

Inclusion criteria are as follows: (1) men or women aged 18 to 65 years; (2) persistent serum HBsAg for ≥6 months; (3) serum HBV DNA ≥2000 IU/mL or ≥10,000 copies/mL; (4) baseline liver fibrosis (liver biopsy) stage F ≥2 (METAVIR system); (5) TCM syndrome type: blood stasis, or blood deficiency with toxic heat retention and (6) no antiviral or antifibrotic therapy for 6 months. Patients are excluded if they have any of the following at enrollment: (1) history of concurrent malignancy, including HCC; (2) baseline liver fibrosis (liver biopsy) stage F <2 (METAVIR system); (3) immunosuppression (organ transplantation or immunosuppressant use); (4) severe alcoholism; (5) serious uncontrollable heart, kidney, lung, endocrine, blood, metabolic or gastrointestinal primary disease, or mental illness; (6) pregnancy or lactation; (7) allergic constitution or allergic to TCM use; (8) no prescribed medication, poor compliance, incomplete data affecting the efficacy and safety of those judgments; (9) unsuitable for this trial according to the researchers or (10) co-infection with hepatitis C or D virus or HIV.

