## Trial status

Patient recruitment for this trial is ongoing. Data collection will continue until the end of November 2018.

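### The week-24 rule for adding adefovir sets two limits, 1 log in IU and 2 log in copies/mL, for a log reduction that is the same number in both units

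*Protocol article*

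**What the plan says.** Study design in the protocol article contains a treatment-modification rule for the double-blind phase. The trigger, applied once 24 weeks have passed, reads "any patients with a reduction in HBV DNA level from baseline <1 log IU or 2 log copies/mL will be treated with". The action it prescribes is to add adefovir dipivoxil, at a daily dose of 10 mg, to entecavir. The rule covers both arms and leaves no discretion.

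Two other places bear on it:

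- Participants and eligibility gives the entry limit in both units: "serum HBV DNA ≥2000 IU/mL or ≥10,000 copies/mL". This pairs absolute levels and implies a fixed conversion factor.
- Follow-up lists the tests: "HBV DNA, hepatitis B surface antigen (HBsAg), anti-HBs, hepatitis B e antigen, anti-HBe, and routine hematological and biochemical tests are performed". It gives no response threshold and no reporting unit.

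The article does not restate or explain the week-24 rule anywhere else.

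**The concern.** The phrase "<1 log IU or 2 log copies/mL" reads as one limit given in two units, in the way the entry criterion is written. That works for an absolute level, where changing units changes the number. It does not work for a reduction on the log scale, where changing units changes nothing. The two numbers are therefore two different response criteria, and the text does not choose between them.

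What is at stake is who receives a second antiviral drug during the double-blind phase. A patient whose HBV DNA has fallen by between 1 and 2 log10 gets adefovir under one limit and not under the other. If centres report in different units, or read the sentence differently, the same virological response leads to different treatment.

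**Working it through.** **Inputs**

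- IU limit: reduction below 1 log (Study design).
- Copies limit: reduction below 2 log (Study design), taking the less-than sign to govern both numbers.
- Conversion factor k: 10,000 / 2,000 = 5 copies per IU (Participants and eligibility).
- Logs are taken as base 10. The cancellation in step 1 holds in any base.

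**Step 1: does the unit affect a log reduction?** Let B be the baseline and W the week-24 level in IU/mL, with copies = k × IU. Then

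log10(kB) − log10(kW) = log10(B/W).

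The factor k cancels. With k = 5, log10(5) = 0.70 is added to both values and drops out of the difference.

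| Fall in IU/mL | Reduction in IU | Same fall in copies/mL (k = 5) | Reduction in copies |
|---|---|---|---|
| 2,000,000 to 200,000 | 1.00 | 10,000,000 to 1,000,000 | 1.00 |
| 2,000,000 to 60,000 | 1.52 | 10,000,000 to 300,000 | 1.52 |
| 2,000,000 to 20,000 | 2.00 | 10,000,000 to 100,000 | 2.00 |
| 2,000 to 100 | 1.30 | 10,000 to 500 | 1.30 |

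The first three rows come out the same with k = 5.6 and k = 5.82, which are assumed values used to test sensitivity to the factor. So 1 log is a 10-fold fall and 2 log is a 100-fold fall, in either unit.

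**Step 2: could the pair be an absolute level converted by mistake?** The sentence says reduction, so this is only a check on where the pair might have come from. One log10 IU/mL is 10 IU/mL = 50 copies/mL, and log10(50) = 1.70, not 2. A gap of a full log would need k = 10, against the article's own 5.

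**Step 3: what each reading tells the investigator to do.** Reading (a) applies each limit to results in its own unit. Reading (b) takes *or* literally, so meeting either limit triggers adefovir.

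| Fall from baseline (log10) | (a) result in IU/mL | (a) result in copies/mL | (b) either unit |
|---|---|---|---|
| below 1 | adefovir | adefovir | adefovir |
| at least 1, below 2 | **no adefovir** | adefovir | adefovir |
| 2 or more | no adefovir | no adefovir | no adefovir |

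For results in copies/mL the readings agree on below 2 log10. For results in IU/mL they conflict in the middle row. Under (b) the IU limit is redundant, since every fall below 1 is also below 2.

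**Step 4: who is in the disputed band?** A fall of at least 1 and below 2 log10 leaves more than 1% and up to 10% of baseline. The first baseline below is the entry floor; the others are illustrative.

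| Baseline (IU/mL) | Week-24 level in the band (IU/mL) |
|---|---|
| 2,000 | above 20, up to 200 |
| 20,000 | above 200, up to 2,000 |
| 200,000 | above 2,000, up to 20,000 |
| 1,000,000 | above 10,000, up to 100,000 |

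Since 2,000 / 0.01 = 200,000, everyone in the band with a baseline of 200,000 IU/mL or more still exceeds 2,000 IU/mL at week 24. Since 2,000 / 0.10 = 20,000, nobody in the band with a baseline below 20,000 IU/mL reaches it. The band is therefore not confined to patients with very little virus left.

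**The case against.** The strongest reply accepts the algebra and disputes the weight.

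- **No inferential consequence is shown.** The rule applies to both arms, and neither the primary end point nor Statistical methods refers to it. This stands: the case rests on a wrongly stated treatment instruction, not on bias, power or error rates.
- **The harm is conditional.** If all centres report copies/mL, both readings give below 2 log10. If all report IU/mL and read the sentence alike, the rule is applied uniformly. The literal *or* can also be carried out as written. All true, but the article gives neither the unit nor the reading, and a reading that leaves one of two printed limits without function is not clearly the intended one.
- **The article condenses a fuller protocol.** The full protocol and the flow chart in Figure 1 were not available, and either might be clearer. So it cannot be concluded that investigators have no usable rule. The objection would meet a complaint that detail is missing; here the article prints a specific rule, and that rule is incoherent.
- **The entry limit is not a response target.** Correct. The 2,000 IU/mL comparison only describes who falls in the band. It does not show that either threshold under-treats or over-treats.

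**Conclusion.** The concern holds. The two printed limits differ by a factor of ten in the fall they require, no constant conversion factor can reconcile them, and nothing else in the article says which applies. The affected patients are those with a week-24 fall of at least 1 and below 2 log10; outside that band every reading agrees. How many patients this is cannot be estimated, because the article gives neither the baseline HBV DNA distribution nor the expected week-24 response.

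The conclusion assumes a constant copies-per-IU factor within a patient and that the less-than sign covers both numbers. Inconsistency between the nine institutions is a possibility that depends on units and readings, not something the article shows. Because the instruction is mandatory and decides on a second antiviral, it should be fixed, although it does not threaten the planned comparison.

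**What to change.** Replace the pair in Study design with one log10 reduction threshold, stated to apply identically to results in IU/mL and copies/mL. The clinical team must confirm whether 1 log10 or 2 log10 was intended; the statistics cannot settle that. If the literal *or* was meant, write it as a reduction below 2 log10 for everyone and delete the IU limit.

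The cost is a one-line amendment and a notice to all centres. The article reports that "Patient recruitment for this trial is ongoing", so at that point the correction could still reach patients who have not yet had their week-24 decision.
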